### Assignment of interventions

#### Allocation sequence generation in RCT 1 and in RCT 2 (Spirit 16a)

Index participants and their household/whānau will be block randomized into RCT 1 at site level to either start the intervention package or continue usual dietary intake for 12 weeks. If there is a second person within the household/whānau who meets the criteria for an index participant, they will be allocated to the same arm as the first index participant, where applicable. Index participants will be randomized using a computer-generated sequence. Household/whānau members will be randomized to the same arm as their corresponding index participant. Index and household/whānau participants will all be randomized once their data have been collected at Visit 2. It is not possible to blind index participants or their household/whānau members to the intervention in RCT 1. Nor is it practical to blind study staff collecting data, however the principal investigator, study statistician and the laboratory team will remain blinded throughout the study and analysis period. Participants will be informed of which arm of RCT 2 they are randomized to after they have completed the RCT 1 intervention.

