### Trial setting (Spirit 9)

The trial settings are four centers in Aotearoa New Zealand: two based at university research units (University of Auckland and University of Otago, Christchurch), one at a community-based traditional Māori meeting place (Tū Kotahi Māori Asthma and Research Trust at Kōkiri Marae in Lower Hutt, Wellington), and the other based at a hospital-based research unit (the Center for Endocrine Diabetes and Obesity Research (CEDOR) in Wellington).

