### Intervention for RCT 2 (Spirit 6b and 11a)

At the end of the 12-weeks of RCT 1, participants randomized to the RCT 1 intervention will immediately be randomized to continuing the opt-in online social support or stopping it. Participants randomized initially to the RCT 1 control will then receive the RCT 1 intervention package described above for 12-weeks and will then be randomized to RCT 2 to either continuing the opt-in online social support or stopping it (Figure 1). All participants will continue to have access to the bespoke study website housing nutrition information.

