#### Details of outcome measures

Clinical assessment including anthropometry, blood sample provision and bioelectrical impedance (BIA) or dual x-ray absorptiometry (DXA) scans will be carried out at the research sites as described in Table 5. Height (cm) will be measured using a wall mounted stadiometer and weight (kg) will be measured using electronic scales. Body composition to include fat mass and lean mass in kg and as %body weight will be measured using either DXA and/or BIA, depending on what is available at the site. Waist circumference (cm) will be measured using a non-stretch tape and blood pressure (BP) (mmHg) will be measured using an automated blood pressure machine. The mean of three measurements of height, weight and waist circumference will be used for these outcome variables. For BP, three measurements will be recorded and the mean of the second and third measurements will be used. Adherence to the dietary pattern will be measured during the intervention period using a 24-h dietary recall and a FFQ (25). The FFQ includes additional questions specifically related to the dietary pattern of interest. The dietary pattern will be assessed using the FFQ data to create a Mediterranean diet adherence score based on the number of serves of olive oil, vegetables, fruit, breads & cereals, legumes, nuts, fish and seafood, eggs, poultry, dairy foods, red meat and sweets that the participants consume (33). A fecal sample will be collected from index participants for future microbiome analysis (Table 5).

**Table 5 tab5:** Schedule of measurements for index participants.

Study period timepoints								
	Eligibility	Enrolment	Intervention and follow up					
	Visit 1 Screening	Visit 2 Baseline Enrolment	Phone contact	Email Contact	Visit 3a Control only	Visit 3b	Visit 4	Visit 5
RCT1 control group		Week 0			Week 12	Week 24	Week 36	Week 64
RCT1 intervention group			Week 2	Week 6		Week 12	Week 24	Week 52
Eligibility screen	✓							
Informed consent	✓							
Medical history	✓							
Education about RCT 1 and RCT 2		✓						
Questionnaires								
Otago short-form FFQ		✓			✓	✓	✓	✓
24 h dietary recall		✓		✓	✓	✓	✓	✓
IPAQ Physical activity		✓			✓	✓	✓	✓
Kaupapa Māori Wellbeing questionnaire		✓			✓	✓	✓	✓
Three factor eating questionnaire		✓			✓	✓	✓	✓
Gastrointestinal symptom rating scale		✓			✓	✓	✓	✓
Self-Evaluation COM questionnaire		✓			✓	✓	✓	✓
Impact evaluation for nutrition and behavior change support					✓	✓	✓	✓
SF-36 quality of life		✓			✓	✓	✓	✓

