Assessments								
Height	✓							
Clinical measurements^a^	✓	✓			✓	✓	✓	✓
Body composition		✓			✓	✓	✓	✓
Current medications	✓	✓		✓	✓	✓	✓	✓
Adverse events			✓	✓	✓	✓	✓	✓
Fasting blood samples ^b^	✓	✓			✓	✓	✓	✓
Fecal sample		✓			✓	✓	✓	

^a^Weight, waist circumference, height, blood pressure in triplicate. ^b^HbA1c, fasting glucose, lipids and metabolites and hormones related to metabolic health Household/whanau members will attend visits 2, 3a/3b, 4, and 5.

A number of sub-studies may be undertaken which include consumer insights including that of Pacific island participants; mixed meal tolerance tests; use of a phone application for the measurement of dietary intake; fecal microbiome analyses. Details of these sub-studies will not be described in this paper.

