### Statistical analyses

The primary analysis will be conducted according to the intention to treat principle. Appropriate data descriptions and plots will be used for all variables. Change from baseline variables will also be described as paired differences but, in general, baseline values of response variables will be used as covariates in analyses rather than analyzing change from baseline. For RCT 1 and RCT 2 and for the index participants, the primary analysis for the primary outcome variable will be Analysis of Covariance (ANCOVA) with the baseline value of the MetSSS as a continuous covariate and the randomized treatment as the main explanatory variable. This strategy will also be used for all continuous outcome variables with the appropriate baseline value of any specific outcome variable as the covariate. The baseline measurement will be just before the relevant randomization. Normal distribution assumptions for residuals will be checked for models of continuous outcome variables and if these are badly violated transformations, such as a logarithm transformation, will be used. For some variables, outlined in Table 4, it is already established that the logarithm transformation is likely to be appropriate. Where appropriate transformations cannot be identified a rank-based procedure, the Mann–Whitney test with the Hodges-Lehmann estimator of location difference, will be used. For the primary outcome variable, the MetSSS, a sensitivity analysis will be a secondary analysis adjusting for possible confounding by important explanatory variables that may have not been evenly distributed by the randomization. These will be as a composite categorical variable for whether medication was changed for any of blood pressure control, glucose management, or lipid control; and separately, for physical activity assessed by the international physical activity questionnaire score. Analysis will be by ANCOVA with these confounding variables in addition to the baseline MetSSS and randomized treatment. Another secondary analysis will be to explore if randomized treatment allocation is associated with different effects in subgroups; using an appropriate treatment by subgroup interaction models. These subgroups are: age, sex, baseline diet adherence score, household size, and whether a household has children. For the continuous variables the analysis of the interaction will be on the continuous scale but for illustrative purposes, and for use in a Forest-like plot, will also be estimated for the first and third quartile of the continuous predictor distribution. Another important secondary analysis will be of all participants treating each household as a cluster and using a Mixed Linear model with baseline measurement and randomized treatment as fixed effects, and household clusters as random effects. If in the event there are very few clusters, the random effect may not be estimable and then this will be equivalent to ANCOVA. The Intraclass correlation coefficient for the clustering effect will be estimated directly from the variance components in the mixed linear models, should a cluster effect be estimable. Categorical and ordinal variables will be analyzed by logistic regression, the latter corresponding to ordinal regression, for the individual participant analysis, and by a Generalized Mixed Linear Model for all participants. There may be other effect modifiers that we will consider but these will be outlined in the Statistical Analysis Plan.

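### RCT 1 is randomised in blocks within site, but its primary ANCOVA leaves site out, so the reported standard error is somewhat too large if site predicts outcome

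*Protocol article*

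**What the plan says.** On allocation, the protocol (Allocation sequence generation in RCT 1 and in RCT 2) says: "Index participants and their household/whānau will be block randomized into RCT 1 at site level". The section on trial setting adds: "The trial settings are four centers in Aotearoa New Zealand". These are two university units, a marae-based community site and a hospital research unit.

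On analysis, the Statistical analyses section gives one primary model for RCT 1 and RCT 2: ANCOVA with baseline MetSSS as covariate and the randomised arm as the factor of interest. It applies the same strategy to the other continuous outcomes. The sensitivity analysis brings in medication change and physical activity: "ANCOVA with these confounding variables in addition to the baseline MetSSS and randomized treatment". The subgroup list is age, sex, baseline diet adherence, household size and presence of children. Site is in none of these. What the section explicitly leaves to the statistical analysis plan is further effect modifiers.

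On the second randomisation, the section Intervention for RCT 2 says that participants who began in the control arm receive the package and "will then be randomized to RCT 2 to either continuing the opt-in online social support or stopping it". No blocking or stratifying factor is named for that step.

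**The concern.** The analysis should normally reflect the restrictions placed on the randomisation. When arms are balanced within each site, the estimated treatment difference is nearly free of between-site variation. A model without site leaves that variation in the residual mean square, so the standard error describes a noisier experiment than the one conducted. Confidence intervals come out too wide, the test rejects too rarely under the null, and some of the power that blocking provides is not used.

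The sites differ in setting and recruit from their own local populations, so it is plausible that site still predicts MetSSS at 12 weeks after baseline is in the model. The documents do not show that it does.

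**Working it through.** **Inputs**

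- Protocol, Sample size: difference 0.4, SD 0.83, 90% power, two-sided 0.05, 184 participants before allowance for non-completion.
- Protocol, Trial setting: four sites, hence three degrees of freedom for site.
- Assumed, not in the documents: the site share s of the outcome variance left after baseline (0.02 to 0.10, with 0.20 as an extreme). For the simulation only: 1:1 allocation, equal sites, blocks of four, baseline–outcome correlation 0.7.

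**Step 1: the plan's own figure.** A two-sample t-test by the noncentral t distribution gives 89.9% power with 91 per arm and 90.2% with 92 per arm. That makes 2 × 92 = 184, as stated.

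**Step 2: the effect of leaving site out.** Let σ² be the outcome variance after baseline.

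- With blocking within site, the variance of the treatment estimate is about 4σ²(1−s)/N.
- The model without site reports about 4σ²/N.
- The reported standard error is therefore too large by 1/√(1−s).
- The actual type I error is 2[1 − Φ(1.96/√(1−s))].
- If the site-adjusted analysis has 90% power, its noncentrality is 1.9600 + 1.2816 = 3.2415 (from unrounded values). Power without site is then Φ(3.2415 − 1.96/√(1−s)).

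| s (assumed) | Standard error too large by | Actual type I error | Power without site (90% with it) |
|---|---|---|---|
| 0 | 0% | 0.050 | 90.0% |
| 0.02 | 1.0% | 0.048 | 89.7% |
| 0.05 | 2.6% | 0.044 | 89.1% |
| 0.10 | 5.4% | 0.039 | 88.0% |
| 0.20 | 11.8% | 0.028 | 85.3% |

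For s = 0.05: 1/√0.95 = 1.026; 1.96 × 1.026 = 2.011; two-sided tail 0.044; 3.2415 − 2.011 = 1.231; Φ = 0.891.

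**Step 3: simulation of the blocked design** (N = 184, 4,000 runs per row). With correlation 0.7, σ² = 0.83² × (1 − 0.49) = 0.3513. The standard error expected from the model without site is √(4 × 0.3513/184) = 0.0874.

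| s | True SE, site out / in | Reported SE, site out / in | Null rejection, site out / in |
|---|---|---|---|
| 0 | 0.0876 / 0.0876 | 0.0874 / 0.0874 | 4.5% / 4.5% |
| 0.05 | 0.0846 / 0.0845 | 0.0875 / 0.0853 | 4.2% / 4.7% |
| 0.10 | 0.0838 / 0.0835 | 0.0875 / 0.0830 | 4.4% / 5.4% |
| 0.20 | 0.0796 / 0.0792 | 0.0878 / 0.0784 | 3.1% / 5.0% |

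The true standard error is almost the same with or without site, so blocking has already secured the precision. Only the reported standard error differs. The Monte Carlo error of a 5% rejection rate is √(0.05 × 0.95/4000) = 0.34 percentage points, so the rejection rates agree with Step 2 within simulation noise.

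**Step 4: the same factor without blocking**, which is all the text supports for RCT 2. At s = 0.20 with the factor left out, the true standard error is 0.0884, the reported one 0.0875, and null rejection 5.1%. The inference is valid. Adjustment would lower the standard error to 0.0788, which is a possible gain in precision and not the repair of an error.

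**The case against.** The strongest defence is that the effect is small, conservative and rests on an assumed quantity. At s of 0.02 or less the simulation shows no visible difference. Even at 0.10, power falls only from 90% to 88.0%. This stands, and it makes the point minor.

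A second defence is that a condensed article may leave covariates to the analysis plan. That does not answer the point. The article names the covariates of the primary and sensitivity models, and what it hands over is further effect modifiers. An analysis plan that followed this text would omit the blocking factor.

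A reader might infer more than the documents support, in four ways:

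- *That RCT 1 loses precision in its estimate.* Step 3 shows that it does not. The fault is in the reported standard error.
- *That the RCT 2 standard error is also wrong because site and RCT 1 arm are omitted.* Blocking is stated for RCT 1 only, and Step 4 shows that omitting an unblocked factor leaves the standard error valid. The RCT 2 baseline is also taken just before the second randomisation, after both sequences have had the package, so it may absorb part of any sequence difference.
- *That mixed DXA and BIA use, "depending on what is available at the site", makes the problem larger for lean and fat mass.* A device offset that is the same at both visits is in the baseline as well as the outcome, and the covariate removes nearly all of it. Assume SD 10 kg and half the participants on each device. With a 4 kg offset and correlation 0.90, what remains is 0.25 × (0.10 × 4)² = 0.04 against 100 × (1 − 0.81) = 19, about 0.2%. With 2 kg and 0.98 it is 0.25 × (0.02 × 2)² = 0.0004 against 3.96, about 0.01%.
- *That the Visit 1 MetSSS should be a second covariate.* Table 5 does schedule the measurements at both visits, but using one pre-randomisation baseline is not an error. Any gain depends on assumed correlations between visits and on a population mean that the documents do not give.

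**Conclusion.** The point holds for RCT 1 as a minor mismatch between the randomisation and the analysis. If site explains 2% to 10% of the variance left after baseline, intervals are about 1.0% to 5.4% too wide and the actual type I error is about 0.048 to 0.039. If site explains none, nothing is lost. The size rests on the assumed s, near-equal allocation within site and the normal approximation; the direction follows from the blocking itself. The treatment estimate is not biased, the false-positive rate is not raised, and neither 184 nor 200 needs to change. For RCT 2, site and RCT 1 arm are optional prognostic covariates unless its randomisation used them.

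**What to change.** - Add site as a fixed effect to the RCT 1 primary ANCOVA and to the RCT 1 ANCOVAs for continuous secondary outcomes.
- State how the RCT 2 randomisation is done, and put any factor used there into the RCT 2 models. Site and RCT 1 arm may otherwise be prespecified as prognostic covariates, but need not be.
- Record the change before unblinding.

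The cost is a line of analysis wording and three degrees of freedom: with 184 participants, the residual degrees of freedom fall from 184 − 3 = 181 to 178. No change to recruitment, allocation or data collection is needed.

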The implementation of the dietary intervention incorporates elements of behavior change science which will be delivered by a multidisciplinary team including trained research staff and allied health care professionals including dietitians. Each site will have one research assistant and a doctoral student to support the clinic visits and arrange for the provision of food. The site staff will also make participants aware of the website and social media support options available to them and will play the website video titled “Introduction to the diet” so participants will be aware of what the dietary pattern entails. The behavioral aspects of the trial aim to support adherence to the NZMedDiet pattern and will include private Facebook groups and Facebook Messenger chats with a dietitian and peer support (online social support) which will be managed by one doctoral student who is a registered dietitian; a behavior change contract signed by participants prior to beginning RCT 1; and educational and motivational resources hosted on a participant facing website and YouTube channel. The website will be developed prior to the trial starting and will have six tabs covering: 1. Research Team, 2. Industry partners, 3. Nutrition support 4. Industry products, 5. Participant frequently asked questions and 6. Contact Us. The Nutrition Support section will link to short videos which will cover an introduction to the diet, goal setting, sample menus and recipes. The Nutrition support will also include multiple one-minute videos recorded by members of the research team, such as those entitled “Planning your shopping,” “Meal Planning,” “Getting to know your ingredients,” “Cooking” and “What to do with leftover food/ kai,” “Understanding your health data,” “Keeping motivated” and “Healthy Holiday Tips.” The behavior change wheel was used to design these resources to overcome identified barriers to the behavior, such as time and cost (17, 18). The participants will be able to interact with the website and online social support as little or as much as they chose.

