#### Implementation (Spirit 16c)

A member of the study team will log into the online system to seek randomization. The allocated arm will be recorded in the participant’s file and in the Site File.

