### Assignment of interventions: blinding

#### Who will be blinded (Spirit 17a)

The Principal investigator, laboratory technicians and study statistician will be blinded.

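### The statement that data collectors cannot practically be blinded is carried over to RCT 2, where no obstacle is described, leaving an avoidable risk of observer bias in the Visit 4 waist measurement

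*Protocol article*

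**What the plan says.** All of this is in the protocol article.

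- **Allocation sequence generation in RCT 1 and in RCT 2 (Spirit 16a).** The section first says "It is not possible to blind index participants or their household/whānau members to the intervention in RCT 1". It continues, without naming a trial stage, "Nor is it practical to blind study staff collecting data". It adds that participants learn their RCT 2 arm once they have finished the RCT 1 intervention.
- **Who will be blinded (Spirit 17a).** For the whole trial: "The Principal investigator, laboratory technicians and study statistician will be blinded". Outcome assessors are not listed for either RCT.
- **Implementation (Spirit 16c).** A study team member obtains the allocation online, and "The allocated arm will be recorded in the participant’s file and in the Site File". No exception is made for the second randomization.
- **Intervention for RCT 2.** Participants are "randomized to RCT 2 to either continuing the opt-in online social support or stopping it". Of the remaining support: "All participants will continue to have access to the bespoke study website housing nutrition information".
- **Intervention for RCT 1.** Online social support consists of private Facebook groups and Messenger chats, "which will be managed by one doctoral student who is a registered dietitian". Each site has a research assistant and a doctoral student, who support clinic visits and arrange the food.
- **Details of outcome measures.** "Waist circumference (cm) will be measured using a non-stretch tape"; the mean of three readings is used. Blood pressure is taken by an automated machine, using the mean of the second and third readings. Weight is taken on electronic scales.
- **Outcomes for RCT1 and RCT2, and Table 4.** MetSSS in index participants is the primary outcome of both RCTs. Its listed components are glucose, triglycerides, HDL cholesterol, systolic blood pressure and waist, and each is also a secondary outcome.

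**The concern.** In RCT 1 it is easy to see why site staff cannot be blinded: they organize food deliveries and show the introductory diet video to one arm only. By the RCT 2 outcome visit that reason has gone. Every participant has had the package, food provision has ended, and the randomized difference lies in an online channel.

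A person placing a tape measure can be influenced, without intending it, by knowing who is still receiving support. Averaging three readings by the same observer reduces random error but not a systematic tendency. The RCT 2 baseline is taken just before the second randomization, so a tendency that begins after allocation affects only the follow-up value, and ANCOVA on baseline does not remove it. RCT 2 participants know their own arm, so blinding the measurer is one of the few protections still available at the clinic visit. Any error would pass in part into the primary score and in full into waist as a secondary outcome.

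**Working it through.** **Step 1: does the RCT 1 reason apply to RCT 2?**

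| Feature | RCT 1 | RCT 2 |
|---|---|---|
| Randomized difference | Food, recipes, meal plans, web education and online support, against usual diet | Continuing or stopping online support |
| Site task described as differing by arm | Arranging food; playing the diet video; pointing to the website and social media | None described |
| Who manages the differing component | Site staff, food providers and the online support manager | The online support manager |
| Website | Intervention arm only | Both arms |
| Outcome visit (Table 5) | Week 12, Visit 3a or 3b | Visit 4 (week 24 or 36), same measurements in both RCT 2 arms |

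Knowing a participant's RCT 1 arm does not reveal the RCT 2 arm, because both RCT 1 groups are re-randomized after receiving the package. The document gives no reason specific to RCT 2 for unblinded measurement.

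**Step 2: which parts of MetSSS are exposed?**

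- Glucose, triglycerides and HDL cholesterol: laboratory values, and the laboratory is blinded.
- Systolic blood pressure: automated device, first reading discarded. Little exposed.
- Waist: manual tape. Exposed.

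The exposure is therefore mainly one component of five.

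**Step 3: the plan's own figures.** Inputs from Sample size (Spirit 14): difference 0.4, SD 0.83, two-sided alpha 0.05, power 90%. The exact t-test calculation gives 91.45, so 92 per arm and 184 in total, as stated. Blinding the assessor changes neither figure.

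**Step 4: how large could the effect on MetSSS be?** The weights are in Figure 2, which is not available here, and the document gives no figure for measurement bias. What follows is an illustration, not an estimate.

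*Shift in the score.* Assume 0.02 to 0.03 MetSSS units per cm of waist and a net difference between arms of 1 to 2 cm from measurement alone:
- lowest: 0.02 × 1 = 0.02, and 0.02 / 0.4 = 5% of the target difference;
- highest: 0.03 × 2 = 0.06, and 0.06 / 0.4 = 15%.

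*False-positive rate.* Assume no true effect, 92 per arm in RCT 2, SD 0.83, and a baseline to follow-up correlation r between 0 and 0.8. Then SE = 0.83 × √(1 − r²) × √(2/92). For a net shift b, the two-sided rejection rate is Φ(b/SE − 1.96) + Φ(−b/SE − 1.96).

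| Assumed net shift b | r = 0 | r = 0.5 | r = 0.7 | r = 0.8 |
|---|---|---|---|---|
| 0.00 | 5.0% | 5.0% | 5.0% | 5.0% |
| 0.02 | 5.3% | 5.4% | 5.6% | 5.9% |
| 0.05 | 6.9% | 7.6% | 8.8% | 10.5% |
| 0.10 | 12.9% | 15.7% | 20.8% | 27.5% |
| 0.20 | 37.2% | 47.1% | 62.9% | 77.8% |

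The two lower rows, 0.10 and 0.20, lie above the 0.02 to 0.06 range. Within that range the inflation is modest.

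**The case against.** The strongest reply is that this is a disclosed design choice. Nothing is contradicted or miscalculated. The sentence on practicality directly follows one confined to RCT 1, so its reach to RCT 2 is read from the section heading and from the trial-wide list of blinded roles. That is fair, and the point is put here as a weakly justified choice rather than an error. The list of blinded roles still leaves assessors unblinded in both RCTs.

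A second reply is feasibility. Two staff are named per site, participants know their arm, household members attend the same visits, and index participants complete an impact questionnaire on behavior change support at Visit 4. Some unblinding is likely. This stands as a limit on what masking can achieve, but partial masking is still better than none. Table 3 gives REDCap as the route for that questionnaire, so the person measuring need not see the answers.

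A reader might also infer several stronger things that the document does not support:
- That bias does enter the primary endpoint. Only a risk is shown, and neither its direction nor its size can be derived.
- That blood pressure and weight are as exposed as waist. The automated device and electronic scales argue against this.
- That sites have no part in the online support. The doctoral student managing it may also be one of the sites' doctoral students, and site staff tell participants about the social media options.
- That the measurer will see the allocation. The arm is recorded in two files, but the article does not say who consults them at Visit 4.
- That the RCT 2 effect is expected to be small. The document gives no RCT 2 effect estimate.

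**Conclusion.** The point holds in limited form. The protocol leaves data collectors unblinded throughout, while the only obstacle it describes belongs to RCT 1. At Visit 4 this creates an avoidable risk of observer bias, mainly through waist, which feeds the RCT 2 primary outcome and is a secondary outcome itself.

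The likely effect on MetSSS is modest: 0.02 to 0.06 against a target of 0.4, if one accepts an assumed weight per cm and an assumed 1 to 2 cm bias, neither of which comes from the document. A shift of 0.05 would give a false-positive rate of 6.9 to 10.5% instead of 5%. Only a considerably larger shift would seriously threaten the primary result. Waist as a secondary outcome would carry the full bias, whatever its size.

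That site staff do not need to know the RCT 2 arm is an inference from the absence of any described task requiring it. The change is worth making because it is cheap. It is an improvement, not the repair of an error.

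**What to change.** For RCT 2:

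1. Release the allocation from the online system only to the person managing the online social support, who then informs participants.
2. Keep the RCT 2 arm out of the file used by measuring staff.
3. Ask participants not to disclose their arm at Visit 4.
4. Have waist, and blood pressure with it, taken at Visit 4 by an existing site staff member without access to the RCT 2 allocation. Where the support manager works at a site, someone else there takes these readings.
5. Amend the sections on allocation sequence generation (Spirit 16a), implementation (Spirit 16c) and who will be blinded (Spirit 17a), so that the statement of impracticality is confined to RCT 1 and RCT 2 measurers are listed as blinded. If this cannot be done at some site, state why.

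The cost is a change of access rights, a request to participants and a short amendment. It uses staff already named and leaves the sample size unchanged. The downsides are that masking will be partial, because some participants will reveal their arm, and that staffing is slightly less flexible at the site where the support manager works.
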